# Study protocol for a single-blind, parallel-group, randomized, controlled superiority trial of intensive versus weekly delivered prolonged exposure for adults with post-traumatic stress disorder

**DOI:** 10.1186/s13063-024-08218-2

**Published:** 2024-06-12

**Keywords:** Post-traumatic stress disorder, Trauma-focused cognitive behavior therapy, Intensive treatment, Massed treatment, Prolonged exposure

## Abstract

**Background:**

Prolonged exposure (PE) therapy is widely recognized as an effective treatment for post-traumatic stress disorder (PTSD) and is often considered one of the primary options for addressing this condition. Nevertheless, a significant proportion of patients (30–51%) fail to demonstrate clinically significant symptom changes. One of the reasons is that a high proportion of patients drop out from treatment, which often lasts for a minimum of 3–4 months. Hence, there is an urgent need for PTSD treatments that can be delivered to decrease dropout rates. A more intensive PE treatment approach has been suggested to decrease dropout rates and in addition achieve faster recovery rates and has shown promising effects on reducing PTSD symptoms but needs to be tested against firsthand treatment.

**Methods:**

This single-blind, randomized controlled trial (*N* = 140) will compare an intensive delivery format of prolonged exposure (iPE) against standard weekly delivered sessions of PE. The primary outcome is change on the Clinician-Administered PTSD Scale for DSM-5 (CAPS-5). Secondary outcomes include self-rated measures of symptoms of PTSD and complex PTSD, depression and quality of life, speed of recovery, cost effectiveness, dropout rates, and adverse events.

**Discussion:**

This study will be the first to compare iPE with first-line treatment in a psychiatric outpatient setting. One of the key strengths of this study lies in its implementation within a clinical setting and the broad eligibility criteria. Additionally, the utilization of gold-standard assessment measures ensures the accuracy and reliability of the outcomes. However, several potential challenges may arise during the study’s execution. These challenges may include difficulties in participant recruitment, ensuring adequate participant retention, adherence to the treatment protocol, and maintaining therapist retention mostly due to recruitment taking place at one single clinic.

**Trial registration number:**

Clinicaltrials.gov NCT05934175. Registered on June 6, 2023. Open Science Framework (OSF) https://osf.io/7qsb3. Registered on September 2, 2023.

## Background {6a}

Post-traumatic stress disorder (PTSD) is characterized by distressing symptoms such as intrusions from the traumatic event, avoidance of trauma reminders, cognitive and mood changes, and arousal symptoms. Its onset is associated with considerable functional and work impairment and psychiatric and medical comorbidity [1–4].

Individual trauma-focused CBT, such as prolonged exposure (PE), is considered a first-line treatment for PTSD in clinical guidelines. Prolonged exposure is typically delivered weekly during a period of 3 to 4 months, which creates a large time window for disruption from unexpected life events, avoidance, or loss of motivation. Despite being a first-line treatment, the response rate for PTSD treatments like PE is only around 60% [5], partly due to high dropout rates, which can reach up to 52% [6]. Patients may hesitate to engage in exposure techniques due to fear, and initial treatment phases might even worsen symptoms before improvement occurs. Intensive treatment formats, characterized by close and continuous therapist-patient contact, offer advantages over standard weekly sessions. They provide more opportunities to address avoidance behaviors, low self-efficacy, and motivational issues. Additionally, the condensed timeframe of intensive treatment may reduce interference from unexpected life events and decrease dropout rates. In summary, intensive treatment approaches may offer a solution to the limitations of standard PTSD therapies, potentially leading to quicker recovery and better resource utilization.

According to a recent systematic review, intensive treatments for PTSD demonstrate potential benefits, such as improved treatment response, faster recovery, and reduced treatment dropout. The review found a large impact on the reduction of PTSD symptoms (weighted mean effect *d* = 1.57, 95% CI [1.24, 1.91]) and notably high rates of treatment completion (5.5% pooled dropout rate across studies) [7]. Nevertheless, the findings should be interpreted with caution, as over 80% of the studies were uncontrolled. Since this review, a randomized clinical trial involving US military personnel and veterans treated with massed or intensive outpatient formats of prolonged exposure therapy resulted in clinically significant reductions in clinician-assessed PTSD symptoms with 50% of participants reaching PTSD diagnostic remission at the 6-month follow-up [8]. Thus, intensive treatment may be an effective treatment format, but its efficacy and cost-effectiveness have not yet been investigated in a psychiatric setting as a head-to-head comparison with first-line treatment for PTSD in individual weekly sessions of prolonged exposure.

In this single-blind, superiority, randomized controlled trial, we will evaluate the efficacy of intensive prolonged exposure compared to first-line treatment (weekly delivered prolonged exposure) for adults with PTSD in a Swedish psychiatric setting. If effective, intensive prolonged exposure could be a welcome addition to available evidence-based options for this target group and reduce dropout.

## Objectives {7}

The main objectives are to investigate the efficacy of intensive exposure-based treatment (iPE) for PTSD in a randomized controlled trial (*N* = 140) comparing iPE with weekly delivered prolonged exposure. The trial will encompass an assessment of health-economic factors from two distinct viewpoints: one from the standpoint of the treatment provider (comprising direct expenses such as healthcare personnel costs) and the other from a more extensive societal standpoint (encompassing indirect expenses such as sick leave). Additionally, we will measure treatment-related transformational processes and factors that can influence treatment results.

The two types of treatment formats will be compared 1 month after treatment completion in each respective treatment arm (primary endpoint) and at the 6-month and 12-month follow-ups regarding clinician-rated PTSD symptom severity by assessors masked to treatment allocation. In addition, comparisons in relation to self-rated symptoms of PTSD and complex PTSD, depression and quality of life, recovery rate, response and remission rates, number of dropouts, cost-effectiveness, adverse events, treatment mediators and moderators, credibility, satisfaction with treatment, and perceived alliance with the therapist will be made. Due to its shorter format, we expect the intensive treatment format to provide a faster response than first-line treatment.

The research questions to be answered within the project are as follows:Is iPE more efficacious than weekly delivered sessions of prolonged exposure regarding reduction of blinded assessor rated PTSD symptom severity 1-month posttreatment in each respective treatment arm?Is iPE more cost-effective than weekly delivered sessions of prolonged exposure at 1 month, 6 months, and 12 months posttreatment?Does iPE lead to less dropout than weekly delivered sessions of prolonged exposure up to 1 month posttreatment?Does iPE lead to more adverse events than weekly delivered sessions of prolonged exposure up to 12 months posttreatment?Does iPE lead to a faster recovery rate than weekly delivered sessions of prolonged exposure up to 12 months posttreatment?Is iPE more efficacious than weekly delivered sessions of prolonged exposure regarding the reduction of self-rated depression and increased quality of life at 1 month, 6 months, and 12 months posttreatment?What is the mechanism of change of prolonged exposure? Does the mechanism of change in iPE and weekly delivered sessions differ?What are the moderators of the treatment effect?Are the therapeutic gains of iPE maintained at long-term follow-up (6 and 12 months after treatment)?

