## Trial design {8}

The trial uses a single-blind (assessors masked to treatment allocation), randomized (1:1), controlled, parallel-group, superiority design comparing intensive prolonged exposure and first-line treatment for adults with PTSD residing in Sweden. We aim to recruit 140 participants who will be assessed before treatment start, during treatment, 1 month after treatment completion in each respective treatment arm (primary endpoint), and at follow-ups 6 and 12 months after treatment completion. The flow chart of the trial is shown in Fig. 1.

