### Intervention description {11a}

#### Intensive treatment (iPE)

The intensive treatment adheres to the original treatment protocol for prolonged exposure [10] with three major exceptions. First, treatment is delivered for five consecutive days followed by three 60-min individual booster sessions dispersed 1, 2, and 4 weeks afterwards. Second, treatment combines individual and group formats. Each patient will receive nine individual sessions focused on confronting the memory of the traumatic event (imaginal exposure and processing) and five group sessions with psychoeducation, breathing retraining, overall rationales, and preparing work with confronting trauma-related situations in the patient’s daily life (in vivo exposure). Starting from day 2, the group sessions shift their focus to the formulation of individually tailored designed exercises for individual implementation during these sessions. Third, there is no assigned homework between treatment days; instead, time is allocated between daily sessions for working on exposure exercises.

The treatment will be delivered for an average of 7 h of treatment each day for five consecutive days. Three individual 60-min booster sessions will be conducted, which will include imaginal exposure, follow-up on in vivo exposure exercises, a comprehensive summary of the treatment and lessons learned, as well as discussions on relapse prevention and planning for continued self-practice. These booster sessions will be dispersed 1, 2, and 4 weeks after the intensive treatment week. The total treatment period is 5 weeks, which encompasses the intensive treatment and booster sessions.

Table 2 shows a typical treatment schedule for the iPE week.

**Table 2 Tab2:** A typical treatment schedule for the iPE week

Monday	Tuesday	Wednesday	Thursday	Friday
**INTRO MEETING** 9:00 – 9:30	**IMAGINAL EXPOSURE SESSION 2** 8:30 – 9:30	**IMAGINAL EXPOSURE SESSION 4** 8:30 – 9:30	**IMAGINAL EXPOSURE SESSION 6** 8:30 – 9:30	**IMAGINAL EXPOSURE SESSION 8** 8:30 – 9:30
**GROUP SESSION 1 PSYCHOEDUCATION, OVERALL RATIONALE, PREPARATION IN VIVO** 9:30 – 11:00	Break 9:30 – 10:00	Break 9:30 – 10:00	Break 9:30 – 10:00	Break 9:30 – 10:00
	**OWN WORK** 10:00 – 11:00	**OWN WORK** 10:00 – 11:00	**OWN WORK** 10:00 – 11:00	**OWN WORK** 10:00 – 11:00
**LUNCH** 11:00 – 12:00	**LUNCH** 11:00 – 12:00	**LUNCH** 11:00 – 12:00	**LUNCH** 11:00 – 12:00	**LUNCH** 11:00 – 12:00

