#### Weekly prolonged exposure

Patients will receive 15 weekly 90-min sessions of individual prolonged exposure for PTSD according to the standard treatment delivery protocol. In session 1, a comprehensive overview of treatment rationale will be provided, along with the selection of the index trauma, which will be the focus of imaginal exposure and breathing retraining. Session 2 will include psychoeducation on trauma and PTSD, along with a rationale for in vivo exposure and the construction of an in vivo hierarchy. In session 3, imaginal exposure including processing for the trauma will commence following an overall rationale of this core treatment component. Starting from session 4 and continuing through session 14, participants will engage in imaginal exposure during the sessions and continue in vivo exposures outside of the therapy sessions. Assigned homework during the treatment weeks will include reading treatment material, practice breathing retraining, listen to recordings of imaginal exposure, and conducting in vivo exercises. Session 15 will include a summary of the treatment and lessons learned, as well as relapse prevention and planning of continued self-practice.

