**Self-rated instruments**									
PCL-5^a^			X	X	X	X	X	X	X
ITQ^a^			X	X	X	X	X	X	X
PHQ-9^b^			X		X	X	X	X	X
EQ-5D^b^			X		X	X	X	X	X
AQoL-6D^b^			X		X	X	X	X	X
TIC-P^b^			X		X	X	X	X	X
NEQ^b^					X	X	X	X	X
CEQ^c^				X					
WAI-SR^d^				X					
Treatment preference	X						X		
SUD-ratings^e^				X	X				

*Abbreviations*: *AQoL-6D* Assessing Quality of Life 6 Dimensions, *CAPS-5* Clinician-Administered PTSD Scale for DSM-5, *CEQ* Credibility/Expectancy Questionnaire, *ITQ* The International Trauma Questionnaire, *MINI* Mini International Neuropsychiatric Interview, *NEQ* Negative Effects Questionnaire, *SUD* Subjective Units of Distress Scale, *TIC-P* Treatment Inventory of Costs in Psychiatric Patients, *PHQ-9* Patient Health Questionnaire, *WAI-SR* Working Alliance Inventory–Short Form Revised

^a^PCL-5 and ITQ are administered daily during the intensive phase of treatment in the I-PE group

^b^PHQ-9, EQ-5D, AqoL-6D, TIC-P, and NEQ are administered immediately after treatment completion, w5 in the I-PE arm and w15 in the weekly delivered PE arm

^c^CEQ is administered after the first individual session in each treatment format

^d^WAI-SR is administered at the third individual session in each treatment format

^e^SUD-ratings are collected each individual treatment session

The primary outcome measure is the gold-standard clinical interview CAPS-5 that assesses PTSD symptom severity and past month diagnosis of PTSD [11] administered at enrollment, 1 month after treatment completion (primary endpoint), and at 6- and 12-month follow-ups. The CAPS-5 total severity score has high internal consistency (Cronbach’s *α* = 0.88) and interrater reliability (intraclass correlation coefficient = 0.91) and good test–retest reliability (intraclass correlation coefficient = 0.78) [11]. In this study, treatment response will be deemed successful if there is a minimum improvement of 10 points on the CAPS-5 scale between baseline and the participant’s last recorded measurement within the baseline to 12-month follow-up period. Remission will be defined as the absence of a PTSD diagnosis and/or a CAPS-5 total symptom severity score below 24, following the criteria set by Blevins et al. [12]. To be categorized as having achieved recovery, participants must maintain their remission status through the subsequent follow-up assessment.

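### Cost-effectiveness and adverse-event horizons are counted from the end of treatment in each arm, so cumulative outcomes summed from baseline cover nominally 10 more weeks in weekly PE than in iPE

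*Protocol article*

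**What the plan says.** The second research question in Objectives {7} is: "Is iPE more cost-effective than weekly delivered sessions of prolonged exposure at 1 month, 6 months, and 12 months posttreatment". The fourth is: "Does iPE lead to more adverse events than weekly delivered sessions of prolonged exposure up to 12 months posttreatment".

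Trial design {8} sets the time origin. Participants are assessed "1 month after treatment completion in each respective treatment arm (primary endpoint), and at follow-ups 6 and 12 months after treatment completion".

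The treatment lengths differ. For iPE, Intervention description {11a} states: "The total treatment period is 5 weeks, which encompasses the intensive treatment and booster sessions". For weekly PE it states: "Patients will receive 15 weekly 90-min sessions of individual prolonged exposure for PTSD".

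Footnote b to Table 3 (Outcomes {12}) applies this to the instruments concerned. PHQ-9, EQ-5D, AQoL-6D, TIC-P and NEQ are "administered immediately after treatment completion, w5 in the I-PE arm and w15 in the weekly delivered PE arm".

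Outcomes {12} assigns AQoL-6D to the QALY calculation and TIC-P to resource use, absenteeism and presenteeism. Adverse events are collected by an open question at each treatment session and by NEQ from the end of treatment onwards. The article gives no common horizon from randomisation for any of these outcomes, and no adjustment for unequal elapsed time.

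**The concern.** A severity score such as CAPS-5 describes a state at one point in time, so assessing it at a fixed interval after each arm's treatment is a defensible choice. Costs, QALYs and event counts are different because they grow with the length of observation. Summed over a longer window in one arm, they differ between arms even when the treatments are identical.

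Two of the listed research questions are affected. In the economic comparison the extra weeks add both QALYs and costs to weekly PE, so the cost side tilts towards iPE and the QALY side towards weekly PE. The net direction depends on the cost accrued per week. In the harms comparison the question is whether iPE causes more events, and a longer observation period in weekly PE tilts the counts towards iPE. The Discussion links the results to implementation in regular care, so these comparisons matter although they are secondary.

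**Working it through.** **Inputs from the article**
- iPE: one intensive week, then boosters ("These booster sessions will be dispersed 1, 2, and 4 weeks after the intensive treatment week"). The last booster falls at 1 + 4 = 5 weeks, which reproduces the stated 5-week period.
- Weekly PE: 15 weekly sessions, so 15 weeks. Footnote b gives the same two values.
- Comparison times: 1, 6 and 12 months after treatment ends.

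**Elapsed time from treatment start** = treatment length + k months, with 1 month = 365.25/12/7 = 4.35 weeks.

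| Comparison | iPE (weeks) | Weekly PE (weeks) | Gap | Ratio |
|---|---|---|---|---|
| 1 month | 5 + 4.3 = 9.3 | 15 + 4.3 = 19.3 | 10 | 2.07 |
| 6 months | 5 + 26.1 = 31.1 | 15 + 26.1 = 41.1 | 10 | 1.32 |
| 12 months | 5 + 52.2 = 57.2 | 15 + 52.2 = 67.2 | 10 | 1.18 |

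**QALYs.** At equal constant utility u in both arms, the extra QALY in weekly PE is u × 10/52.18 = 0.19u. The article gives no utilities. For an assumed u of 0.5 to 0.8 this is 0.096 to 0.153, about 0.10 to 0.15 QALY, from length alone.

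**Costs.** With an equal weekly cost c, weekly PE accrues 10c more. The incremental ratio between two identical treatments would then be 10c / (10u/52.18), about 52c/u per QALY, which is entirely an artefact of the windows.

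**Adverse events.** The only stated horizon is 12 months after treatment. Person-time in weekly PE is 67.2/57.2 = 1.175 times that in iPE, up to about 18% more. Recorded events would rise by the same proportion only under a constant rate and detection proportional to time.

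**How firm the 10 weeks is.** Under Treatment variables, early recovery requires at least six sessions with imaginal exposure. In weekly PE this starts at session 3, so the earliest such session is 3 + 6 − 1 = 8, or week 8. Against a full iPE course the gap is then 8 − 5 = 3 weeks, or 3/52.18 = 0.06u QALY, if follow-up is counted from actual completion. If it is counted from the weeks in footnote b, the gap stays at 10.

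**Coverage of a common window.** Week 52 precedes the nominal 12-month visit by 57.2 − 52 = 5.2 weeks in iPE and by 67.2 − 52 = 15.2 weeks in weekly PE. It is therefore inside nominal follow-up in both arms. A wait between randomisation and treatment start, whose length is not stated, would only move those visits later.

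**The case against.** The strongest reply is that the research question says when cost-effectiveness is assessed, not how costs and QALYs are accumulated. The analysis plan is a separate file, the trial commits to CHEERS reporting, and accumulation rules usually sit in such a plan. This stands to the extent that the bias is conditional: it arises if the quantities are summed from baseline to the stated visits. A reader might infer that the reported ratio is bound to be biased, and the article does not establish that. It does, however, state the horizons and the origin, and these give unequal windows if followed as written. Summing only from the end of treatment would equalise the windows but leave out the treatment period. That would sit badly with Objectives {7}, which counts provider personnel costs, and with the collection of adverse events at each treatment session.

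On harms, a reader might infer about 18% more recorded events in weekly PE, or twice as many at 1 month. Neither is supported. The article makes no 1-month adverse-event comparison. Ascertainment is largely by occasion: iPE has 9 individual, 5 group and 3 booster sessions (17 in all), weekly PE has 15, and NEQ follows the same four post-treatment points in both arms. Under Adverse event reporting and harms {22} participants may also report at any time, so some dependence on elapsed time remains, but its size cannot be fixed from the article. Events during a longer course are also partly a real feature of that format.

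It is also fair that 10 weeks is a nominal figure and that early finishing in weekly PE narrows it.

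**Conclusion.** The point holds in conditional form. The stated horizons, counted from each arm's treatment completion, give weekly PE up to about 10 more weeks of observation at each economic comparison and at the end of the adverse-event window, with less where participants finish early. If costs and QALYs are summed from baseline, length alone adds up to about 0.19u QALY (0.10 to 0.15 for the assumed utilities) and 10 weeks of costs to weekly PE. The net sign for cost-utility cannot be determined from the article. For adverse events the firm statement is up to about 18% more person-time; the excess in recorded events may be smaller.

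These figures assume nominal treatment lengths and time counted from treatment start. The delay from randomisation and the TIC-P recall period are not stated. A reader might extend the point to CAPS-5 at 1 month, but that outcome is a severity score at a point in time, not a sum over time, and this argument does not reach it.

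**What to change.** For costs, QALYs and adverse events, set time zero at randomisation and state one main comparison over a common window ending at week 52. Interpolate AQoL-6D to week 52 and pro-rate TIC-P costs to the same window. Report adverse events to that week, and also per unit of person-time. Reword the two research questions to match, and carry the same definition into the analysis plan and the health-economic plan.

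Treat earlier common-week comparisons as supportive only. iPE has no AQoL-6D or TIC-P visit between about weeks 9 and 31, so values in that interval would rest on interpolation.

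The change needs no new visit. Its downside is some interpolation, and pro-rating that depends on the TIC-P recall period, which should be stated alongside it. The CAPS-5 primary endpoint and its timing stay as they are.

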## Trial design {8}

The trial uses a single-blind (assessors masked to treatment allocation), randomized (1:1), controlled, parallel-group, superiority design comparing intensive prolonged exposure and first-line treatment for adults with PTSD residing in Sweden. We aim to recruit 140 participants who will be assessed before treatment start, during treatment, 1 month after treatment completion in each respective treatment arm (primary endpoint), and at follow-ups 6 and 12 months after treatment completion. The flow chart of the trial is shown in Fig. 1.

